## Abstract

**Introduction:**

Traditional early warning scores (EWSs) use vital sign derangements to detect clinical deterioration in patients treated on hospital wards. Combining vital signs with demographics and laboratory results improves EWS performance. We have developed the Hospital Alerting Via Electronic Noticeboard (HAVEN) system. HAVEN uses vital signs, as well as demographic, comorbidity and laboratory data from the electronic patient record, to quantify and rank the risk of unplanned admission to an intensive care unit (ICU) within 24 hours for all ward patients. The primary aim of this study is to find additional variables, potentially missed during development, which may improve HAVEN performance. These variables will be sought in the medical record of patients misclassified by the HAVEN risk score during testing.

**Methods:**

This will be a prospective, observational, cohort study conducted at the John Radcliffe Hospital, part of the Oxford University Hospitals NHS Foundation Trust in the UK. Each day during the study periods, we will document all highly ranked patients (ie, those with the highest risk for unplanned ICU admission) identified by the HAVEN system. After 48 hours, we will review the progress of the identified patients. Patients who were subsequently *admitted* to the ICU will be removed from the study (as they will have been correctly classified by HAVEN). Highly ranked patients *not admitted* to ICU will undergo a structured medical notes review. Additionally, at the end of the study periods, all patients who had an unplanned ICU admission but whom HAVEN *failed to rank highly* will have a structured medical notes review. The review will identify candidate variables, likely associated with unplanned ICU admission, not included in the HAVEN risk score.

**Ethics and dissemination:**

Approval has been granted for gathering the data used in this study from the South Central Oxford C Research Ethics Committee (16/SC/0264, 13 June 2016) and the Confidentiality Advisory Group (16/CAG/0066).

**Discussion:**

Our study will use a clinical expert conducting a structured medical notes review to identify variables, associated with unplanned ICU admission, not included in the development of the HAVEN risk score. These variables will then be added to the risk score and evaluated for potential performance gain. To the best of our knowledge, this is the first study of this type. We anticipate that documenting the HAVEN development methods will assist other research groups developing similar technology.

**Trial registration number:**

ISRCTN12518261

Strengths and limitations of this studyThe study methodology is in accordance with the STrengthening the Reporting of OBservational studies in Epidemiology guidelines.We describe a method that combines risk score testing with a structured medical notes review conducted by a clinical expert for the iterative improvement of a digital system that quantifies risk for unplanned intensive care unit admission in all ward patients.To the best of our knowledge, this is the first study of this type.

## Background

### Introduction

Early warning score (EWS) systems, such as the National Early Warning Score, combine abnormalities in patient vital signs into an aggregate score.^1^ This score triggers a clinical response when a threshold is exceeded. Despite wide-scale adoption of EWS systems, significant clinical patient deterioration on hospital wards still occurs.^1 2^ Additionally, high numbers of false alerts lead to alert ‘fatigue’ and inefficient use of response teams.^3^ Adding additional clinical information to such systems, such as laboratory results and comorbidities, improves specificity.^4–12^ However, identifying and adding new variables requires a systematic approach to avoid needless complexity.^13^

We have developed a system to predict the risk of unplanned intensive care unit (ICU) admission (within 24 hours) for patients on general medical and surgical wards. It is called the Hospital Alerting Via Electronic Noticeboard (HAVEN).^14^ To identify potential variables for inclusion in HAVEN, we used a modified Delphi process and a systematic literature review.^15^ Those identified variables that were available within the electronic patient record (EPR) were extracted from data sets comprising all patients admitted to two National Health Service (NHS) trusts (a trust is a legal entity that provides goods and services for the purposes of the provision of hospital, community and/or other aspects of patient care).^12^ We then used a machine learning method^16^ to select the optimal combination of variables for the HAVEN risk score. In contrast to EWS systems, HAVEN was not designed to produce alerts. Instead, HAVEN provides a list of patients in the hospital, ranked from most to least at risk of requiring ICU admission. The intent is that HAVEN will improve patient safety by informing the use of clinical response teams.

### Aims and objectives

The primary aim of this study is to discover additional candidate variables, not recognised during the data-driven derivation process, that would improve the performance of the HAVEN risk score. We will review the medical records of *misclassified* patients, that is, patients ranked highly by HAVEN but who were not admitted to the ICU; or patients who were never ranked highly by HAVEN but had an unplanned ICU admission.

### The HAVEN risk score

The HAVEN risk score is calculated using both *static* and *dynamic* variables extracted in real time from the EPR.

Static variables refer to patient-level data available at admission: age, gender, comorbidities (classified according to the Elixhauser comorbidity index^17^) and Hospital Frailty Risk Score.^18^ As diagnostic coding in the UK occurs after a patient has been discharged, the comorbidity index and frailty scores are calculated using a patient’s admissions over the previous 2 years. Score performance in patients with no previous admissions (and potentially undocumented comorbidities) will be evaluated separately.

Dynamic variables refer to measurements taken repeatedly during hospital admission, that is, laboratory results and vital signs. The HAVEN risk score is currently updated according to the most recent measurements of: albumin, bilirubin, C reactive protein, haemoglobin, platelets, white cell count, potassium, sodium, urea, creatinine, heart rate, systolic blood pressure, respiratory rate, body temperature, a neurological status assessment using either the Alert-Verbal-Painful-Unresponsive scale or the Glasgow Coma Scale, peripheral oxygen saturation from pulse oximetry (SpO_2_) and the estimated fraction of inspired oxygen.^19^ A patient’s HAVEN score is re-calculated each time a new dynamic variable is received by the system and the score is further adjusted for the time since hospital admission.

## Methods

The study will be reported according to the STrengthening the Reporting of OBservational studies in Epidemiology guidelines.^20^

### Design and setting

This is a prospective, observational, cohort study conducted at the John Radcliffe Hospital, part of the Oxford University Hospitals NHS Foundation Trust in the UK. The John Radcliffe Hospital is a tertiary hospital with over 800 beds and serves a population of over 650 000 people, who are generally more affluent and with higher life expectancy than the national average.^21^

## Data collection

Data collection will occur during 4, full, non-consecutive weeks in 2019. The notes review will be undertaken by a senior critical care physician. Patients who are discharged or die during the study period will have these details recorded. They will remain in the analysis data set.

### Participants

#### Eligibility criteria

Emergency and elective adult patients (16 years or over) admitted to medical, surgical, observational or short-stay wards will be eligible for inclusion. We will exclude patients for whom a score cannot be generated (ie, those with no recorded vital sign or laboratory measurements).

#### Sample size

We will sample two subgroups of patients:

False High Rank (FHR).False Low Rank (FLR).

The FHR group will consist of patients ranked highly by HAVEN but who were not admitted to the ICU. To identify this group, we will record the five highest-ranked patients on the HAVEN system at 09:00 each morning of the study. After 48 hours, we will remove any patients who were subsequently admitted to the ICU. The remaining patients’ records will be reviewed.

The FLR group will be identified at the end of the study and consist of all patients who had an unplanned ICU admission during the study period and were not present in any of the daily high-ranking groups. These patients’ records will also undergo a medical notes review.

The study will run for 4 non-consecutive weeks with expected recruitment of between 130 and 150 patients.

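### The rule for clearing high-ranked patients accepts any ICU admission found at 48 hours, while HAVEN targets unplanned admission within 24 hours, so some misclassified patients may go unreviewed

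*Protocol article*

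**What the plan says.** **The score's target.** The Abstract (Introduction) says that HAVEN uses the record "to quantify and rank the risk of unplanned admission to an intensive care unit (ICU) within 24 hours for all ward patients". The Background repeats that it was developed to "predict the risk of unplanned intensive care unit (ICU) admission (within 24 hours) for patients on general medical and surgical wards".

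**The rule for high-ranked patients.** The top five are recorded at 09:00 on each study morning. The Abstract (Methods) then states: "After 48 hours, we will review the progress of the identified patients". Those found to have gone to ICU "will be removed from the study (as they will have been correctly classified by HAVEN". The Sample size section puts it this way: "After 48 hours, we will remove any patients who were subsequently admitted to the ICU". Those who remain form the FHR group and have their notes reviewed.

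**The rule for missed patients.** The Sample size section limits the FLR group to unplanned ICU admissions in patients who were on none of the daily top-five lists.

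**Who is eligible.** The Eligibility criteria admit "Emergency and elective adult patients (16 years or over"), on surgical as well as medical wards.

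**The concern.** The removal rule differs from the score's target in two ways.

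- **Event.** It accepts ICU admission of any kind. Elective surgical patients are eligible, so a planned ICU stay is possible and would be credited to HAVEN. The FLR rule names unplanned admission, so the two groups are defined on different events.
- **Time.** Status is taken at 48 hours, twice the 24-hour horizon, with no reason given. An admission on the second day counts as a success for a list that predicted only the first.

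The primary aim is to find missing variables by reading the notes of misclassified patients, so the definition of misclassified is the sampling frame. The review also looks for factors behind decisions on ICU admission, and late or planned admissions bear on that. Any variables found go back into the development of a score whose target is unplanned admission within 24 hours, so the cases reviewed should be labelled against that target.

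**Working it through.** **Step 1. Follow each type of patient through the rules as written.**

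- *Listed, unplanned admission within 24 hours of that list.* Target met. Removed as correct. No problem.
- *Listed on day 1 and again on day 2, unplanned admission 24 to 48 hours after the first list.* This is within 24 hours of the second list, so the target is met for that list. Removal is right.
- *Listed on day 1 only, unplanned admission 24 to 48 hours later.* Target not met for any list. Removed from FHR as correct, and barred from FLR because the patient was once listed. Notes not read.
- *Listed, planned ICU stay by 48 hours.* Not the target event. Removed from FHR. Barred from FLR on both conditions. Notes not read.
- *Listed, not in ICU by the 48-hour check.* Stays in FHR and is reviewed.
- *Never listed, unplanned admission.* In FLR and is reviewed.

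The gap is therefore confined to the third and fourth types.

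**Step 2. Size of the list.** 5 patients × 7 days × 4 weeks = 140 list entries, the midpoint of the stated 130 to 150 patients. These are entries, not distinct patients, and the count leaves out repeats, removals and FLR patients. Because the weeks are non-consecutive, the last morning of each has no study list the next day. That is 4 × 5 = 20 of the 140 entries for which relisting the next morning cannot occur within the study.

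**Step 3. How many entries could be affected (all rates assumed).** Let a be the share of entries with an ICU admission by 48 hours, and s the share of those that are not unplanned within 24 hours of that list. Wrongly removed = 140 × a × s.

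- Low: a = 5%, s = 10%: 7 removed, 0.7 wrongly (about 1).
- Middle: a = 20%, s = 25%: 28 removed, 7 wrongly. FHR would be 119 entries instead of 112.
- High: a = 30%, s = 50%: 42 removed, 21 wrongly.

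**Step 4. The late share under simple hazards (also assumed).** With 24-hour risk p and constant hazard, the 48-hour risk is 1 − (1 − p)², and the share arising after 24 hours is (48-hour risk − p) / 48-hour risk.

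- p = 10%: (0.19 − 0.10) / 0.19 = 47%
- p = 20%: (0.36 − 0.20) / 0.36 = 44%
- p = 30%: (0.51 − 0.30) / 0.51 = 41%

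If the hazard changes on day 2 by a factor k, the 48-hour risk is 1 − (1 − p)^(1+k). At p = 20%, k = 0.5 gives (0.284 − 0.20) / 0.284 = 30%, and k = 0.3 gives (0.252 − 0.20) / 0.252 = 21%.

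**Step 5. Correct for relisting.** Steps 3 and 4 count each list entry separately. If a fraction r of the late unplanned admissions were on the next morning's list and admitted within 24 hours of it, only (1 − r) of them are misclassified on every list. The document gives no r. The score is recalculated with each new measurement, so a deteriorating patient may well stay in the top five. The figures above are upper limits for what is lost through lateness.

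**The case against.** The case against has real weight.

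- **The 48-hour window may be deliberate.** The Aims section defines misclassified simply as ranked highly and not admitted to ICU. Nothing says that FHR must reuse the 24-hour horizon, and the sentence strictly fixes only when status is checked. A patient who reaches ICU at 30 hours was plausibly at high risk, so a margin before calling the ranking false is defensible. This stands as a possible rationale, but the protocol does not give it, and it does not explain the missing restriction to unplanned admissions.
- **Unplanned may be implied.** The Abstract describes the listed patients as those at highest risk of unplanned admission, so the shorter wording that follows could be shorthand in a condensed article. That is possible. But the same section uses the full term for FLR, and the contrast recurs in the Abstract, the Aims and the Sample size section.
- **Daily lists rescue many late admissions.** This stands in full and limits the point to patients who were not relisted.
- **No accuracy figure is estimated from these groups.** This also stands. The work is a thematic notes review, and candidate variables are tested afterwards in the development pipeline.

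A reader might infer that two-fifths or more of the removed patients are really false positives, or that a performance estimate is biased. The document supports neither. The first rests on an assumed constant hazard counted per list entry, and no performance estimate from these groups is described.

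**Conclusion.** The mismatch is in the text. Followed as written, the removal rule drops two kinds of patient who are misclassified against HAVEN's stated target: those with a planned ICU stay, and those with an unplanned admission more than 24 hours after their last listing but before the 48-hour check. The FLR rule then prevents their recovery, in a study whose purpose is to read the notes of misclassified patients.

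The size cannot be derived. The range of about 1 to 21 of 140 entries rests on assumed admission rates and off-target shares and ignores relisting. The true number of patients may be small, and the number of planned stays among top-five patients is not given. The loss is of informative cases from a qualitative sample, not bias in a stated estimate. The point is of moderate importance: worth correcting before data collection, but not a threat to the study as a whole.

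**What to change.** Amend the Sample size section, and the matching sentence in the Abstract, as follows:

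1. Restrict removal to unplanned ICU admissions, so that both groups use the same event.
2. Record the time and type (planned or unplanned) of each ICU admission among listed patients.
3. Treat a patient as correctly classified if an unplanned ICU admission occurs within 24 hours of any 09:00 list on which they appeared. This keeps relisted patients as true positives.
4. Keep other unplanned admissions up to 48 hours, and review them as a separate late-event category instead of removing them.

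The 48-hour check can stay as the time at which status is ascertained. The cost is a few lines of wording, two extra data items per ICU admission and a few more notes reviews. Because the late events are held apart, a team that regards 48 hours as a fair margin can still leave them out of the FHR themes.

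### The False Low Rank rule sets no time window or order between a 09:00 listing and the ICU admission, so some patients not ranked highly before admission are kept out of the missed group

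*Protocol article*

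**What the plan says.** Protocol article, Sample size. High rank is captured once a day: "we will record the five highest-ranked patients on the HAVEN system at 09:00 each morning of the study". For FHR there is a time link: "After 48 hours, we will remove any patients who were subsequently admitted to the ICU". FLR is identified at the end of the study as "all patients who had an unplanned ICU admission during the study period and were not present in any of the daily high-ranking groups". No interval or sequence is attached to that definition.

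Elsewhere in the same article:
- The Abstract and Introduction give the prediction target as unplanned ICU admission within 24 hours.
- The HAVEN risk score section says the "HAVEN score is re-calculated each time a new dynamic variable is received by the system", so ranks can change through the day.
- Aims and objectives describes the same group as "patients who were never ranked highly by HAVEN but had an unplanned ICU admission". The Abstract (Methods) likewise speaks of a failure to rank highly, with no mention of a time of day.
- Data collection runs over four full, non-consecutive weeks.

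**The concern.** The primary aim is to find candidate variables by reading the notes of misclassified patients, and FLR is the group meant to hold the under-ranked ones. Whether a patient was under-ranked can only be judged against rank in some period before the ICU admission. The FLR rule instead looks at every list in the study, including lists long before the admission and lists after it. One early or late appearance moves the patient out of FLR and, at most, into FHR, which represents the opposite error.

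A second issue is one of wording and assessability. The aims promise a group that was never ranked highly, but the data described are one reading a day. Some patients may have had no reading at all while on a ward and scored.

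**Working it through.** **The stated figure.** Expected recruitment is 130 to 150. No derivation is given. Taking 7-day weeks, 4 × 7 = 28 lists and 28 × 5 = 140 list places, which lies inside that range. It counts places, not distinct patients, before those admitted are removed and without FLR. It is therefore consistent with the range but does not confirm how it was obtained, and it says nothing about how many patients the FLR rule affects.

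**How far the rule reaches.** Each ICU admission is compared with all 28 lists. Away from the start of a study week, a 48-hour window before admission contains 2 lists and a 24-hour window contains 1. So 28 − 2 = 26 of the lists that can bar a patient from FLR lie outside 48 hours, and 28 − 1 = 27 lie outside the score's own horizon.

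**Constructed cases, applying the wording as written.**
1. *Listed early, admitted late.* Listed at 09:00 on day 1 and on no later list; ICU at 14:00 on day 6, which is 5 × 24 + 5 = 125 hours after listing. Not admitted within 48 hours, so kept in FHR. Absent from the lists 29 and 5 hours before admission, yet barred from FLR by the day 1 list. The same holds if the admission falls in a later study week.
2. *Listed only afterwards.* Never listed; ICU on day 2; back on the ward and listed on day 5, with no further ICU admission. Barred from FLR by a list that came after the event, and kept in FHR.
3. *Between 24 and 48 hours.* Listed at 09:00 on day 1, not on day 2; ICU at hour 40. Removed from FHR by the 48-hour check and barred from FLR, so not reviewed. This is a success on the FHR window but not on the 24-hour target; the article uses both periods without reconciling them.
4. *No list to consult.* Reaches a ward at 11:00; ICU at 22:00 the same day; not listed on any other day. Labelled FLR, although no 09:00 list could have included the patient. Observational and short-stay wards are eligible, so brief stays are in scope. The exclusion of patients for whom no score can be generated does not cover someone scored later that day.

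No other section of the article supplies a window, an order or a reclassification step.

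**Size.** The article gives no ICU admission counts, admission times or durations of high rank. The frequency of each case cannot be computed.

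**The case against.** The strongest defence is that the 09:00 snapshot is an openly stated choice, used for both groups, for a tool designed as a ranked list and not as an alert. The study is a hypothesis-generating review with no error rate estimated from FLR. Patients in cases 1 and 2 still have their notes read as FHR, under the same structured review. Any spurious candidate variable is later tested in the score development pipeline (Discussion, Main findings). All of this stands, and it limits the consequences. It does not supply the missing window: case 1 is still grouped under the opposite error, and later testing cannot recover a candidate that was never raised.

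A reader might infer several stronger things that the document does not support:
- *That a patient who rose into the top five after 09:00 was ranked correctly and is mislabelled as FLR.* A patient scored at 09:00, outside the top five, and in ICU at 22:00 was ranked low 22 − 9 = 13 hours before admission, inside the 24-hour horizon. A later rise does not undo that, and such patients may be useful cases.
- *That a known share of FLR is mislabelled.* If admission times were even over the day and a patient held a top-five rank without a break for the last L hours, the chance that no 09:00 list falls in that time is 1 − L/24: 75% at 6 hours, 50% at 12, 25% at 18. L is assumed, and the result is not a proportion of the FLR group.
- *That about 5% of study time has no prior list.* 4 × 9 = 36 of 28 × 24 = 672 hours (5.4%) precede a week's first list if weeks start at midnight. If they start at 09:00 the figure is 0, and the article does not state the start time.
- *That rank at every moment could be used instead.* The article documents only the recorded 09:00 top five; stored continuous ranks are not mentioned.

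**Conclusion.** The concern holds in a limited form. The FLR definition lacks a time window and an order of events, so it excludes some patients whom HAVEN did not rank highly before their ICU admission. It is out of step with the 24-hour target and with the 48-hour FHR check. A 09:00 list also cannot establish the wording used in the aims, and patients with no usable list before admission are called missed when their ranking is unknown.

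This follows from the wording alone and needs no numerical assumption. Its size is unknown. The consequence is misgrouped cases, and in the 24-to-48-hour case an unreviewed one, within a thematic review. No test or estimate is biased, and the article does not show that the themes would be distorted. The point is of moderate weight, worth correcting before FLR is assembled at the end of the study because the remedy is nearly free.

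**What to change.** - Define FLR per unplanned ICU admission, as absence from every 09:00 top-five list in the 48 hours before that admission. This matches the FHR window.
- Flag admissions where the patient was listed 24 to 48 hours before but was not on the list in the last 24 hours, so that the score's own horizon stays visible.
- Delete the clause that excludes anyone on any daily list, so that an earlier or later listing does not bar a patient from FLR.
- Place admissions with no 09:00 list in the window, taken while the patient was on a ward and scored, in a separate not-assessable category. This also handles admissions before a study week's first list.
- In the Abstract and in Aims and objectives, describe the group as not in the 09:00 top five.
- If continuous ranks happen to be stored, report as a descriptor whether FLR patients entered the top five after 09:00. Do not use this to define the group.

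Cost: a wording change and a comparison of ICU admission times with lists already recorded. There is slightly more bookkeeping, some patients will count in both groups for different events, and the size of FLR will change a little: it gains cases such as 1 and 2 and loses the not-assessable ones.
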